### Recruitment procedure

Parents are recruited primarily through advertisements on online interest sites and social media platforms. Specifically, posts targeted for a local parent audience are advertised weekly on Facebook and Instagram. Additionally, print advertisements are placed at recreation centers, health care centers, children’s recreation classes, and coffee shops every few months. Pamphlets are also offered at biweekly booths at local community markets and family-oriented events. To ensure diversity of the study population, the city was systematically stratified into regions, and facilities from each region were randomly selected and contacted for recruitment as per a previously refined recruitment strategy. Recruitment also takes place on a referral basis whereby current participants are invited to pass study information to others. Finally, incentives for participation include honoraria subsidizing the cost of the activity (up to a total of $80) as well as assistance with childcare costs if needed (up to $25 weekly).

Recruitment is ongoing across the length of the study. Because enrollment takes place in waves that align with seasons for adult sport leagues/programs, those who demonstrate interest are placed on a wait-list to enroll during the uptake for the next wave.

Those interested in taking part are invited to contact the researchers via email or phone. If interest in the study is expressed, potential participants are sent additional study details by email. At the next stage of the enrollment process, potential participants are formally screened over the phone with a recruitment officer or the project coordinator. If they meet the eligibility criteria, they are booked for a baseline assessment or alternatively placed on a wait-list, depending on the timing of the next wave.

### Randomization, allocation, and blinding

Randomization is performed by the project coordinator using Excel Sheet Randomization at a 1:1:1 allocation ratio. A research assistant then prepackages envelopes containing certificates that indicate condition assignment along with a list of potential ideas and resources for that condition. A second research assistant who is blind to participants’ condition presents the participants with their randomized allocation.

### Outcome measures

#### Primary outcome measures

##### Change from baseline to 3 months in parental psychosocial outcomes

Assessments of psychosocial outcomes in all three groups are collected through online questionnaires (available on SurveyMonkey) and occur at three time points: baseline, 6 weeks, and 3 months.

##### Quality of life

Psychosocial outcomes are primarily assessed using the 12-item Short Form Health Survey (SF-12) [33, 34], which measures health-related quality of life on a range of functional domains, including vitality, social functioning, and overall well-being. The domains assessed in the SF-12 have prior application in the sport domain [27, 35]. The SF-12 has been validated for adult populations, and there is established evidence for the reliability of scores derived from the instrument [34].

#### Secondary outcome measures

##### Psychosocial outcomes and psychosocial distress

Additional quality of life outcomes are assessed via the Satisfaction With Life Scale, which has established reliable and valid test scores [36] and has been used in prior sport research [37]. Given our parent sample, we also measure relationship satisfaction with the Relationship Assessment Scale, which has shown adequate validity and reliability [38, 39], and parental stress with the previously validated Parental Stress Scale, which has shown a high level of internal consistency [40]. Finally, family functioning is assessed using the self-report Family Inventory Version II, which measures familial health/competence, conflict, cohesion, leadership, and emotional expressiveness [41].

##### Sport commitment and sport participation

Parents are also assessed on the constructs of the Sport Commitment Model [20] at three time points: baseline, 6 weeks, and 3 months. The Sport Commitment Model [20] is measured by the associated sport commitment questionnaire with the adjusted measures for adult samples relevant to parents of children [26, 42]. Previous sport commitment research among adult fitness participants has shown the questionnaire to have acceptable validity and reliability in the measurement of sport commitment, enjoyment, involvement alternatives, personal investments, social constraints, and involvement opportunities [24]. The questionnaire wording was slightly modified in order to be framed for both sport and physical activity.

Additionally, at the final 3-month measurement, condition adherence/sport participation is assessed with a study-created item, “How was your attendance for your condition (team sport, individual sport, or personal time)?” with possible answers of “did not adhere at all,” “missed over half the sessions (at least 6),” “missed 3–4,” “missed 1–2,” and “did not miss any sessions.” An additional item assesses reasons for missing sessions with responses including common barriers for parents, such as “too tired,” “couldn’t get childcare,” “work commitments,” and “family commitments.” Last, four items rated on a scale from 1 (strongly disagree) to 5 (strongly agree) asks participants the extent to which their condition was enjoyable, beneficial, or challenging and how much they looked forward to their weekly activity. Condition adherence/sport participation is also complemented by a phone-assisted report of attendance at the 6-week assessment and an in-person report at the final 3-month interview.

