Can participation in the team sports and individual sports conditions be explained by the constructs of the Sport Commitment Model?We hypothesize that participation will be predicted by sports commitment as per the tenets of the Sport Commitment Model. Commitment will be predicted primarily by enjoyment (+), social constraints from family obligations/involvement alternatives (−), and social involvement opportunities/personal investments (+).Can group differences among these motivational and behavioral outcomes be explained through a mediation model?We propose that the covariance of the assigned conditions on psychosocial outcomes will be explained by sport participation. In turn, the covariance between participation and assigned conditions will be explained by salient underlying motives from the Sport Commitment Model. In particular, enjoyment will explain the differences between both sport conditions, but the better psychosocial outcomes from team sports will be explained by the additional involvement opportunities of friendship and social interaction.Is there a seasonal, gender, dual/single parent, age of child, or type of sport difference across primary outcomes by assigned condition?Differences in season, gender, age of child, and type of sport are exploratory research questions. It is possible that both sport conditions may have participation lowered by weather conditions in the winter. Men may participate in sport more due to lower childrearing expectations; however, there is currently limited research to support this conjecture. Similarly, younger children may impact sport participation because of the considerable care needs of young children. Finally, it is possible types of sport could differ in their psychosocial outcomes for reasons such as the structure or environment of participation.

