### Analysis strategy

Missing data will be inspected to determine the appropriate imputation procedures [43], and normality of all variables will be checked to determine whether any transformations are required. To determine whether psychosocial outcomes change over time similarly for all three conditions (i.e., to address objective 1), a level 1 model will be specified wherein the intercept (i.e., value of the outcome at baseline) will be allowed to vary randomly (i.e., vary across participants) and the slope for the linear trend will be constrained to be fixed (i.e., the same across participants), controlling for any significant covariates at level 2. Additionally, dummy variables will be created for condition (team sports: 1 = yes or 2 = no; individual sport: 1 = yes or 2 = no; control: 1 = yes or 2 = no) at level 2, with the team sport and individual sport variables being added to the model to predict the intercept and slope at level 1. In doing so, the control group is compared with the other two groups to determine if baseline psychosocial outcomes are similar across conditions and whether the change is similar across conditions. Follow-up analyses will be conducted for the group comparison. To determine whether participation within the team and individual sport conditions is explained by the Sport Commitment Model constructs (i.e., secondary objective 1), a time-varying covariate analysis will be used. For example, within the team sport condition, participation will be predicted by a level 1 model that includes a random intercept, fixed slope, and the time-varying Sport Commitment Model constructs. The same will then be done for the individual sport condition. To determine whether the change in the underlying motives explains the potential change in sport participation during the intervention similarly for all three groups (i.e., to address secondary objective 2), a time-varying covariate mediation analysis approach will be used following the procedure outlined by Krull and MacKinnon [44] for level 1 mediation. Briefly, the analyses needed to establish mediation will treat the underlying motives as time-varying covariates at level 1 of the model. Then, the dummy-coded condition variables will be entered at level 2 to determine if the mediation relationships are similar across groups. Finally, to determine whether there is a seasonal, gender, or sport type (within team or individual) difference across the primary and secondary outcomes (i.e., to address secondary objective 3), each variable will be entered into the various models at level 2 to predict the intercepts and slopes at level 1. Doing so will determine if they impact the change in the various outcomes across time.

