Finally, participants in the individual sport choice condition are provided with a customized handout of our environmental scan of available adult individual sports programs in Greater Victoria (maintained and updated) and asked to choose one of these available options. “Individual sport” is defined as a physical activity performed or completed by an individual with a structured rule set of competition or progression toward an outcome or goal. Individual sports include rowing, running, cycling, swimming, and rock climbing.

Upon allocation, participants are asked to begin their activity as soon as possible (i.e., register for a team sport, choose an individual sport or “personal time” activity, and commence weekly sessions). Participants in both sport conditions are asked to keep track of their attendance in the program. After the initial 6 weeks, participants are sent follow-up questionnaires to complete via email. Contact is made initially with a phone call by the research assistant to answer any questions the participants may have about their experiences over the last 6 weeks. A phone-assisted report of sport participation over the past 6 weeks is also ascertained at this time. A similar protocol is followed at the 3-month mark; however, participants are asked to come to the laboratory to partake in a brief wrap-up interview and an end-of-trial questionnaire (*see* Fig. 1 for schedule of interventions and assessments). To assist study retention, we offer to subsidize the program chosen by participants with a maximum $80 contribution toward registration (or the personal time activity of choice for the control participants) as well as a maximum $25-per-week contribution toward childcare when needed. Participants must complete the study in order to receive the honorarium.

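### For secondary question 2, sport participation is measured only as attendance at the assigned condition, and the planned mediation model contains no psychosocial outcome

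*Protocol article*

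**What the plan says.** All references are to the protocol article.

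- **Hypothesis.** Present research aims and hypotheses, secondary question 2: "We propose that the covariance of the assigned conditions on psychosocial outcomes will be explained by sport participation". Motives from the Sport Commitment Model are then to explain the link between condition and participation.
- **Measure.** Sport commitment and sport participation: at 3 months, "condition adherence/sport participation is assessed with a study-created item". The item is "How was your attendance for your condition (team sport, individual sport, or personal time". The five answers run from no adherence, through "missed over half the sessions (at least 6"), missed 3–4 and missed 1–2, to "did not miss any sessions". They are the same for every arm.
- **Other reports.** The same section adds: "Condition adherence/sport participation is also complemented by a phone-assisted report of attendance at the 6-week assessment", and an in-person report at 3 months. The intervention section describes the 6-week call as a report of sport participation, not of attendance. It also states: "Participants in both sport conditions are asked to keep track of their attendance in the program".
- **Control activity.** The intervention section requires that personal time not be physically active.
- **Analysis.** For secondary objective 2, the Analysis strategy tests "whether the change in the underlying motives explains the potential change in sport participation during the intervention similarly for all three groups". It uses level 1 mediation with motives as time-varying covariates, then enters condition at level 2 to see whether the relationships are alike across groups. For secondary objective 1, the participation model is fitted in the team arm and then in the individual arm.

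**The concern.** Adherence to the assigned arm and participation in sport are different variables, and the article gives them one label and one item. In a sport arm they nearly coincide. In the control arm they are close to opposites, since full adherence there means regular time that must be inactive. A mediator that is supposed to carry the effect of being assigned to sport has to differ between arms because of sport. This one differs only if parents in one arm keep their appointments better than parents in another.

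Two further problems sit beside it. The analysis described for objective 2 stops at participation, so the stated hypothesis about psychosocial outcomes is not tested. The answer scale also omits one possible count of missed sessions. At stake is the trial's explanation of why sport helps, if it does. The primary SF-12 comparison between arms does not depend on any of this.

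**Working it through.** The article gives no adherence rates or mediation figures, so there is no stated number to reproduce. The check sets the text side by side and adds one illustration.

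**1. What the item records in each arm**

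| Parent | Sport sessions through the condition | Answer on the item |
|---|---|---|
| Team sport, attended all | all | top category |
| Individual sport, attended all | all | top category |
| Control, kept all personal time | none | top category |

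**2. Size of the problem (illustration).** Score the answers 0 (no adherence) to 4 (none missed). The scoring and the distributions below are assumptions. Mean = sum of score × proportion.

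- Sport arms, proportions 0.10, 0.10, 0.20, 0.35, 0.25: 0 + 0.10 + 0.40 + 1.05 + 1.00 = 2.55.
- Control adheres equally: mean 2.55, contrast 2.55 − 2.55 = 0.00.
- Control adheres better (0.03, 0.05, 0.12, 0.35, 0.45): 0 + 0.05 + 0.24 + 1.05 + 1.80 = 3.14, contrast 2.55 − 3.14 = −0.59.
- Control adheres worse (0.30, 0.20, 0.20, 0.20, 0.10): 0 + 0.20 + 0.40 + 0.60 + 0.40 = 1.60, contrast 2.55 − 1.60 = +0.95.
- Control sport participation scored 0 instead: contrast 2.55 − 0 = 2.55 in every case.

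The sport arms are identical throughout. Only control compliance moves the contrast on the item. The values depend on the assumptions, but the zero contrast under equal adherence does not.

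**3. What the planned model does with it.** The objective 2 analysis covers all three groups. In the sport arms it would relate motives to sport attendance. In the control arm it would relate motives framed for sport and physical activity to attendance at inactive personal time. Comparing these relationships across groups compares different dependent variables.

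**4. Hypothesis against model**

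- Hypothesis: condition → participation (with motives behind it) → psychosocial outcome.
- Model: motives → participation, compared across conditions.

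The last variable of the hypothesis does not appear in the model described.

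**5. Answer scale.** Counts covered: 0, 1–2, 3–4, 6 or more, and no adherence. The count 5 has no category.

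**6. Who can still be asked.** From Results: 161 of a target 240 enrolled, 127 with 6-week data, 109 finished. Not yet enrolled: 240 − 161 = 79. Enrolled but without 3-month data: 161 − 109 = 52, some of whom may have dropped out. Upper limit for a new 3-month question: 79 + 52 = 131. Upper limit for a new question at the 6-week contact: 240 − 127 = 113.

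**The case against.** **No scoring rule is given.** The article lists answers, not a derived variable. Arm is known for every parent, so an analysis plan that is not shown could separate adherence from sport. This is fair, and it rules out saying that control parents will certainly be analysed as full participants. It does not remove the problem. Setting controls to zero would assume that they did no sport, which the item does not ask, and would leave no variation in that arm for a level 1 model. What is missing is a measurement, not only a derivation.

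**The 6-week phone report may be a true sport measure.** It may be, on the wording in the intervention section. The measures section calls it attendance under the merged label, and neither section names it as the mediator.

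**Stronger readings that the text does not support.**

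- A reader might infer that question 1 fails too. It is fitted within each sport arm, where attendance at the condition is attendance at the assigned sport. Only the gap at 5 missed sessions reaches it.
- A reader might infer that a planned indirect effect will have the wrong sign. The Analysis strategy does not describe a path from condition through participation to outcome, so no planned estimate is reversed. The negative contrast above is one assumed case.
- A reader might infer that participation has no baseline value and no repeated format. The baseline questionnaire includes sport behaviour items, and an attendance report is taken at both 6 weeks and 3 months.
- A reader might say that 6 missed sessions is not over half. That needs a session count, which the article does not give: 6 of 12 is 50% and 6 of 13 is 46%, but 6 of 11 is 55% and 6 of 10 is 60%.

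**Conclusion.** The point holds for secondary question 2. As written, participation is not measured separately from adherence. A three-arm contrast on the item would show differential compliance: zero under equal adherence, and anywhere from −0.59 to +0.95 in the assumed cases, against 2.55 with control sport scored 0. The last figure assumes that control parents do no sport. Separately, the model described for objective 2 does not test the stated hypothesis, because it has no psychosocial outcome. The missing category for 5 missed sessions is a small, certain flaw that affects question 1 as well, wherever the item is used.

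This should be corrected, but it concerns a secondary question. The primary comparison stands, and question 1 is otherwise sound on this point.

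**What to change.** 1. At the existing 6-week and 3-month contacts, ask all three arms the same question: the number of sport sessions done in the period. Count any sport that meets the article's team or individual definitions. Do not limit it to organised sessions, which could miss self-chosen running, cycling or swimming.
2. Use that count as sport participation in question 2. Keep attendance at the assigned condition as a separate adherence variable, and describe the 6-week report the same way in both sections.
3. Close the gap in the answer options so that 5 missed sessions has a category.
4. For question 2, specify a model from condition to participation and motives at 6 weeks to psychosocial outcome at 3 months, adjusted for baseline values.

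The cost is one added question, one edited answer option and analysis wording. The main drawback is coverage. The 109 parents already finished have only the existing item and any phone or interview records. The new question reaches at most 131 of 240 at 3 months and at most 113 at the 6-week contact. The mediation result should be reported with that limit.

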### Design

This study is a three-arm, parallel design, single-blind, randomized controlled trial. Written informed consent is obtained from participants before study enrollment. Participants are then assigned to one of three groups for a duration of 3 months: team sport choice condition, individual sport choice condition, or personal time control condition. Primary outcome measures in all three groups are assessed at baseline, 6 weeks, and 3 months. The design, conduct, and reporting of the trial has and continues to follow Standard Protocol Items: Recommendations for Interventional Trials (SPIRIT) guidelines [29] and will conform with Consolidated Standards of Reporting Trials (CONSORT) guidelines [30]. A SPIRIT checklist is provided as an Additional file and the SPIRIT diagram is included as Fig. 1. The randomized controlled trial is registered with the clinical trials registry maintained by the National Library of Medicine at the National Institutes of Health (ClinicalTrials.gov identifier NCT02898285).

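### The 3-month attendance item offers no answer for exactly five missed sessions, and its label for over half mixes a proportion with a fixed count

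*Protocol article*

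**What the plan says.** The item is described under Secondary outcome measures, Sport commitment and sport participation. It is timed as follows: "at the final 3-month measurement, condition adherence/sport participation is assessed with a study-created item". The question names all three conditions, "How was your attendance for your condition (team sport, individual sport, or personal time", and has one common set of five answers. The first is for a complete lack of adherence, and the other four read "missed over half the sessions (at least 6),” “missed 3–4,” “missed 1–2,” and “did not miss any sessions".

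The number of sessions is not given. The Intervention description section has participants "choose an individual sport or “personal time” activity, and commence weekly sessions", and the Design section says "Participants are then assigned to one of three groups for a duration of 3 months".

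The item is not the only attendance measure. The same outcome section says it is "complemented by a phone-assisted report of attendance at the 6-week assessment and an in-person report at the final 3-month interview". The Intervention description adds: "Participants in both sport conditions are asked to keep track of their attendance in the program".

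**The concern.** A single-choice item needs answers that cover every possible count and do not contradict themselves. This one skips a count in the middle of its range. It also defines its 6-or-more category twice, once as a share of sessions and once as a number, without stating the total that would make the two agree.

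What is at stake is secondary. The item is named as an assessment of condition adherence/sport participation. Under Analysis strategy, participation is the modelled outcome for secondary objective 1 and features in the mediation analysis for secondary objective 2. Under Present research aims and hypotheses, participation is also proposed to explain the effect of condition on psychosocial outcomes. Misclassified attendance that enters these analyses adds error to them. It does not touch the primary outcome, which is the SF-12 compared by assigned condition.

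**Working it through.** **Inputs.** The answer categories come from Sport commitment and sport participation, weekly frequency from Intervention description, and the 3-month duration from Design. The session count n is not stated. I take about 12–13 as an assumption (weekly sessions over 3 months) and show n = 6 to 14.

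**Step 1: reproduce the label's own equation.** Over half of n sessions begins at floor(n/2) + 1 missed. Setting this equal to 6 gives floor(n/2) = 5, so n = 10 or 11. For n = 12 or 13 it begins at 6 + 1 = 7. Six missed is then 6/12 = 50% or 6/13 = 46%.

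**Step 2: place five and six missed sessions for each n.**

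| Sessions n | Over half begins at | Five missed | Six missed |
|---|---|---|---|
| 6–7 | 4 | over half, but below 6 | both parts of label fit |
| 8–9 | 5 | over half, but below 6 | both parts of label fit |
| 10–11 | 6 | no answer fits | both parts of label fit |
| 12–13 | 7 | no answer fits | count fits, proportion does not |
| 14 | 8 | no answer fits | count fits, proportion does not |

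For n = 6 or 7, four missed satisfies both the 3–4 answer and the over-half wording. No n from 6 to 14 makes the item both exhaustive and consistent. Read as counts alone, the answers cover 0, 1–2, 3–4 and 6 or more, so five is the only count left out.

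**Step 3: how often five might occur (illustration only).** Assume each session is missed independently with probability p. With n = 12, P(exactly 5 missed) = C(12,5) × p^5 × (1 − p)^7, where C(12,5) = 792.

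- p = 0.2: 0.053
- p = 0.25: 0.103
- p = 0.3: 0.158
- p = 0.4: 0.227

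At p = 0.1 it is 0.004. With n = 13 the values at p = 0.2, 0.3 and 0.4 are 0.069, 0.180 and 0.221. The protocol gives no miss rate, and misses caused by work, childcare or dropout are unlikely to be independent. These figures show only that the gap need not be trivial.

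**The case against.** The strongest reply is that this is a small wording flaw in one secondary item and that other attendance reports are already planned. Much of that stands. The 6-week phone-assisted report and the 3-month in-person report may supply the missing count, and both sport arms are asked to track attendance. The item is asked once, whereas Analysis strategy models participation with a random intercept, a slope and time-varying covariates. It therefore cannot by itself be that repeated outcome, and the article does not say which attendance source enters the model.

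Three stronger readings are tempting, and the documents do not support them.

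- A reader might infer that everyone in the middle of the attendance range must misreport. Only those who missed exactly five lack an answer. A parent who missed six of 12 or 13 meets a contradictory label but can answer by the count.
- A reader might infer that attendance is not comparable across programmes. That needs session counts to differ, and none are given. Weekly sessions over 3 months imply similar counts. Limited team seasons and self-chosen programmes make differences plausible, but that is inference.
- A reader might infer, because only the sport arms are asked to track attendance, that control adherence rests on 3-month recall. The outcome section does not restrict the phone and in-person reports to the sport arms. The Intervention description calls the phone report one of sport participation, so coverage of controls could be clearer, but recall alone is not shown.

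What the reply does not remove is the defect in the item. An analysis plan cannot restore an answer that participants were never offered.

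**Conclusion.** The point holds in limited form. The omission of five missed sessions follows directly from the printed answers and needs no assumption when they are read as counts. The mismatch between over half and at least 6 depends on the number of sessions. It is present at the 12–13 implied by weekly sessions over 3 months and absent only at 10 or 11.

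The consequence is misclassification, on this item, of parents who missed exactly five sessions, with an adjacent category the likely choice. Its frequency is unknown. The range of about 5% to 23% rests on an assumed 12 independent sessions and miss rates of 20% to 40%. The effect is confined to the adherence/participation measure relevant to secondary objectives 1 and 2, and the complementary reports can reduce it. It should be corrected because the correction is nearly free, not because it threatens the trial's main result.

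**What to change.** For remaining participants, make the answers exhaustive and purely count-based, for example by adding an answer for five missed and dropping the over-half wording. Asking for the number of sessions scheduled and the number attended would serve equally well.

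For participants already assessed, take the count where available from the 6-week phone-assisted and 3-month in-person reports, in all arms. State that these reports cover the personal time arm.

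The cost is one reworded online item and a rule for mapping older records to the revised categories. According to Results, 161 of the planned 240 had been recruited, leaving 240 − 161 = 79 to enrol, and 109 had completed the 3-month measures. A change would therefore leave data from two forms of the item, so the mapping rule should be written down before analysis. A weekly attendance log for controls, or analysing the proportion attended, would be optional and is not needed to repair the item.
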